## Abstract

**Background:**

Compression therapy is routinely recommended after the thermal ablation of varicose veins (VVs), but the optimal duration of treatment remains controversial. International guidelines acknowledge the lack of evidence to support a specific duration of compression therapy (grade 2C). In current clinical practice, the selection of therapy options (1–3 months or even longer) rely mainly on the clinical judgment of physicians, with significant variability in patient compliance and quality of life. This trial aims to determine the effects of different compression durations (1, 3, and 6 months) on recurrence, quality of life, and complications at 12 months after surgery.

**Methods:**

This will be a prospective, multicenter, randomized, parallel-group trial. This study will include 600 patients with great saphenous vein insufficiency (C2–C6) treated with endovenous radiofrequency or laser ablation at 7 high-volume centers. The participants will be randomly assigned to the following groups at a 1:1:1 ratio: the one-month (OM) group, which will wear class II compression stockings (23–32 mmHg) for 1 month after surgery; the three-month (TM) group, which will wear compression stockings for 3 months; and the six-month (SM) group, which will wear compression stockings for 6 months. All the groups will wear the same compression stockings and follow the same instructions for wearing the stockings. The primary outcome is the recurrence of VVs at 12 months; the secondary outcomes include the closure rate of the great saphenous vein, disease-specific quality of life assessed by the Aberdeen Varicose Vein Questionnaire (AVVQ), the Chronic Lower Limb Venous Insufficiency Questionnaire (CIVIQ) score, the Venous Clinical Severity Score (VCSS), the incidence of postoperative complications (pain, ecchymosis, paresthesia, deep vein thrombosis, etc.), and patient compliance. The follow-up times are 1, 3, 6, and 12 months after surgery.

**Discussion:**

This trial fills a key gap in evidence concerning the optimal duration of compression therapy after endovenous thermal ablation and the effect of providing optimal compression therapy on recurrence. The results of this study will provide high-level evidence for a standardized duration of compression therapy and contribute to updated future clinical guidelines.

**Clinical trial registration:**

chictr.org.cn, identifier ChiCTR2100049550.

## Introduction

Varicose veins (VVs) of the lower extremities affect 15%–20% of adults worldwide and can lead to serious complications, such as pain, edema, skin damage, and ulcers (1, 2). Endovenous thermal ablation procedures [radiofrequency ablation (RFA), endovenous laser ablation (EVLA)] are recommended as first-line therapy options (3–5). Postoperative compression therapy using elastic stockings is considered the essential treatment for VVs, which can reduce postoperative pain, edema, and bruising and may prevent the postoperative recanalization of VVs (6, 7). Although compression therapy is recommended by guidelines as a necessary treatment after thermal ablation, the optimal duration of compression therapy remains controversial, and strong evidence is lacking (8–10). Recent guidelines have only clarified the necessity of compression therapy, but still not specify the optimal duration of compression therapy (5). Therefore, there is considerable variability in the use of compression therapy after the thermal ablation of VVs among different centers and regions: some centers recommend 1 month of compression therapy after thermal ablation, whereas others recommend 3 months or longer (11–13). Long-term compression therapy is often recommended, especially for patients with venous ulcers (C5-6). It is undeniable that the long-term use of compression stockings can result in leg discomfort and skin irritation, which could lead to poor compliance in patients who use compression therapy for a long period (14, 15), especially in early stage with C2-3. Therefore, recent studies have focused mainly on short-term (several days/week) regimens and the short-term results of compression therapy (16–18), including parameters such as immediate pain relief and return to work after surgery. A recent study reported that there was no difference in the great saphenous vein (GSV) closure rate in patients who received short-term compression therapy during a 6 month follow-up (10). Owing to the lack of long-term follow-up data, evaluating the effects of different durations of compression therapy on the postoperative recurrence of varices and the quality of life (QoL) of patients is very difficult. Additionally, owing to hemodynamic abnormalities such as GSV and deep venous reflux, short-term compression therapy may have limited effects on patients’ QoL scores and symptom improvement. Thus, we believe that determining the optimal duration of compression therapy is crucial for the evaluation of patient-centered efficacy (QoL scores and long-term recurrence), and few high-quality randomized controlled trials (RCTs) have evaluated the medium- and long-term outcomes of compression therapy after surgery in patients with VVs (10). The latest clinical guidelines confirm that the optimal duration of compression therapy after the thermal ablation of VVs is still based on clinical judgment rather than evidence-based medical data (5). This multicenter RCT aims to evaluate the differences in VV recurrence rates and QoL scores at 12 months after thermal ablation surgery among three compression therapy strategies and provide new evidence for the optimal duration of compression therapy after thermal ablation.

### Objectives

The primary objective of this study is to determine the recurrence of VVS at 12 month after thermal ablation in patients with different durations of compressure therapy, assessed by duplex ultrasound scanning and clinical physical examination. The secondary objectives are the saphenous vein (GSV) closure rate at 12 month, the closure failure is defined by a segment of the reopen vein ≥5 cm by ultrasound. The VCSS, AVVQ, CIVIQ scores are compared among the three groups at baseline, 1, 3, 6, and 12 month, as well as the pain scores [using the Visual Analog Scale (VAS)] at baseline, 24 h, and 1 month after surgery. Postoperative complications are recorded in three groups, and the compliance of compressure therapy is investigated.

## Methods

The SPIRIT reporting guidelines were followed in the development of this protocol (19).

### Study design

This will be a prospective, multicenter, open-label, randomized, three-arm trial with a 12 month follow-up (Figure 1). The SPIRIT checklist is provided in Supplementary File S1.

**Figure 1 fig1:**
[figure not shown]
The trial flowchart. VCSS, Venous Clinical Severity Score; AVVQ, Aberdeen Varicose Vein Questionnaire; CIVIQ, Chronic Lower Limb Venous Insufficiency Questionnaire; OM, one-month; TM, three-month; SM, six-month; VAS, Visual Analog Scale.

### Participants

Patients with VVs of the lower extremities will be included in this trial, all patients will diagnosed via clinical examination and duplex ultrasound examination at all centers, and all patients will sign an informed consent form.

### Inclusion criteria

An age ranging from 18 to 70 years.The presence of primary, symptomatic unilateral or bilateral lower limb VVs (CEAPs C2-C6).A GSV reflux duration >0.5 s on duplex ultrasound.A GSV diameter of 3–12 mm (thigh segment).Scheduled to undergo RFA or EVLA (1,470 nm laser) of the GSV.The ability and willingness to provide informed consent.

### Exclusion criteria

A history of ipsilateral VV intervention (surgery, ablation, or sclerotherapy).A history of deep vein thrombosis (DVT) or post-thrombotic syndrome (PTS).The presence of significant peripheral arterial disease (ABI < 0.8).Severe infection of the treatment site.A known allergy to compression stocking material;The presence of severe medical comorbidities precluding surgery/follow-up (e.g., uncontrolled cardiac failure, terminal illness).Pregnancy or lactation.Participation in another conflicting clinical trial.The inability to comply with compression therapy or follow-up schedule.

### Randomization and blinding

Eligible, consenting patients will be randomized at a 1:1:1 ratio to one of the following groups: the one-month group (OM group, elastic stockings for 1 month), three-month group (TM group, elastic stockings for 3 months), and six-month group (SM group, elastic stockings for 6 months) using a central, computer-generated, stratified block randomization sequence via a secure randomization-generated web-based system. Patients and physicians cannot be blinded owing to the nature of the intervention (duration visible to the patients). The outcome assessors (Duplex ultrasound technicians, QoL questionnaire administrators) and statisticians will be blinded to group allocation.

### Interventions

#### Thermal ablation

All participants will undergo standardized RFA (ClosureFast™, Medtronic) or EVLA (Eufoton 1,470 nm ring laser Biolitec) of the incompetent GSV under ultrasound guidance and tumescent anesthesia (20), which will be performed by surgeons with experience in performing >200 ablation procedures. In brief, the GSV trunk was cannulated just below the knee under ultrasound guidance, and then radiofrequency catheter (ClosureFast, Medtronic, United States) was inserted 2 cm below the saphenofemoral junction and ablated at a temperature of 120 °C for 20 s per segment. The same technique was used in the EVLA group by using a radial laser fiber (1,470 nm, Eufoton, Italy) at power: 10 W and energy: 70 J/cm. The VVs below the knee was treated by using ultrasound-guided foam sclerotherapy and a pin stripping (mini-phlebectomy) procedure.

#### Postoperation compression

All participants will have identical Class II (23–32 mmHg) full-length graduated compression stockings applied in the operating room immediately after ablation, and the patients will be asked to wear the stockings during the day and night for 48 h and then during waking hours (following the protocol). The durations of compression therapy will be as follows:

OM group: Wear stockings during waking hours for 1 month after surgery.TM group: Wear stockings during waking hours for 3 months after surgery.SM group: Wear stockings during waking hours for 6 months after surgery.Compliance will be monitored via patient diaries and questionnaires.

### Primary outcome

The primary outcome is the recurrence of target VVs at 12 months (21, 22). New recurrence is defined as the postoperative appearance of VVs that did not exist in the VV area in the lower limbs before surgery; primary recurrence is defined as the reappearance of VVs that existed in the VV area before surgery during follow-up. Both types of recurrence are defined as postoperative recurrence.

### Secondary outcomes

The secondary outcomes are as follows.

#### Closure rate of target veins

The target vein occlusion rate at 12 months is defined as ultrasound-confirmed recanalization of the treated GSV segment (≥5 cm), and the occlusion rate will be calculated as the number of target venous closure cases/total number of cases.

#### QoL assessment

Disease-specific QoL at baseline and at 1, 3, 6, and 12 months after surgery will be measured by the AVVQ (total scores ranging from 0–100, with 100 indicating the worst QoL) (23).

#### Venous Clinical Severity Score (VCSS)

All patients will be asked to complete the VCSS questionnaire to assess the severity of venous disease features at baseline and at 1, 3, 6, and 12 months after surgery. The VCSS questionnaire consists of 10 questions, each scored as 0 (none), 1 (mild), 2 (moderate), or 3 (severe), with a total score ranging from 0 to 30, with 30 representing the most severe venous disease (24).

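### If the VCSS form has the standard compression-use item, the 0–30 total counts the randomised treatment as disease severity, clearly so for OM versus SM at month 3

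*Protocol article*

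**What the plan says.** The VCSS section of the protocol article describes the instrument as follows: "The VCSS questionnaire consists of 10 questions, each scored as 0 (none), 1 (mild), 2 (moderate), or 3 (severe), with a total score ranging from" … The range then given is 0–30, and a higher total means worse disease. The section also says who supplies the answers: "All patients will be asked to complete the VCSS questionnaire to assess the severity of venous disease features". The visits are baseline and months 1, 3, 6 and 12.

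The Objectives section makes the score a between-arm outcome: "The VCSS, AVVQ, CIVIQ scores are compared among the three groups at baseline, 1, 3, 6, and 12 month". The Statistical analysis section puts it in a linear mixed model adjusted for baseline values, center, CEAP class and time. Neither section removes an item from the total.

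The randomised difference is how long stockings are worn: 1 month (OM), 3 months (TM) or 6 months, the last stated as "SM group: Wear stockings during waking hours for 6 months after surgery". On blinding, the Randomization and blinding section says: "Patients and physicians cannot be blinded owing to the nature of the intervention (duration visible to the patients"). It lists ultrasound technicians, quality-of-life questionnaire administrators and statisticians as blinded.

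**The concern.** An outcome that compares treatment arms should not contain the treatment. The standard 10-item VCSS has an item that grades how much compression the patient uses, and more use adds points. In most venous trials this matters little, because compression is the same in every arm. Here compression duration is the only thing randomised.

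If the item is on the trial's form, two arms with the same veins, skin and symptoms will differ on the total at any visit where one arm is in stockings and the other is not. The arm with the longer assignment looks worse while it wears them and appears to improve when it stops. An interim VCSS difference could then be read as a clinical effect of duration when it only records who was told to wear stockings.

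A second, smaller limitation is that the patients complete the score and know their allocation. A blinded administrator does not change what an unblinded patient answers.

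**Working it through.** **1. The plan's own figure.** 10 items × a maximum of 3 = 30. This reproduces the stated range, so all ten items are summed. It does not show what the items ask.

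**2. Who is assigned stockings at each visit** (Postoperation compression section set against the visit schedule):

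| Visit | OM | TM | SM |
|---|---|---|---|
| Month 1 | end of period | wearing | wearing |
| Month 3 | off | end of period | wearing |
| Month 6 | off | off | end of period |
| Month 12 | off | off | off |

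The article gives no recall period or visit window, so there are two ways to read the end-of-period cells:

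- If they count as wearing, month 1 shows no difference, month 3 separates OM from TM and SM, and month 6 separates SM from OM and TM.
- If they count as off, month 1 separates OM from TM and SM, month 3 separates SM from OM and TM, and month 6 shows no difference.

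Only OM versus SM at month 3 differs under both readings. Month 12 differs under neither.

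**3. Size of the shift.** Let *c* be a wearer's score on the item (a non-wearer scores 0), *w* the share wearing in the arm assigned stockings, and *v* the share still wearing off schedule in the other arm. Then shift = *c* × (*w* − *v*). The documents give none of these values. All are assumptions, with *c* from 1 to 3.

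| Assumed wear | *w* − *v* | Shift, *c* = 1 to 3 |
|---|---|---|
| 100% and 0% | 1.0 | 1.0 to 3.0 points |
| 80% and 10% | 0.7 | 0.7 to 2.1 points |
| 50% and 20% | 0.3 | 0.3 to 0.9 points |

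**4. Would a shift of that size be noticed?** For a simple two-arm comparison at one visit, the chance that the shift alone gives two-sided p < 0.05 is about Φ(shift ÷ [SD × √(2/n)] − 1.96). Take n = 160 to 200 per arm (200 planned; 200 × 0.80 = 160 after the stated 20% withdrawal) and an assumed SD of 2 to 4 points. For example, with shift 0.7, SD 3 and n = 200, the standard error is 3 × √(2/200) = 0.30, and Φ(0.7/0.30 − 1.96) is about 65%. Over the whole grid:

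- 100% and 0% wear: 61% to nearly 100%
- 80% and 10% wear: 35% to nearly 100%
- 50% and 20% wear: 10% to 99%

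**5. After the change.** Nine items × 3 = 27. The compression item then contributes nothing to the between-arm difference, whatever the adherence or visit timing.

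**The case against.** The strongest objection is that the protocol never lists the ten items. A reader might infer that the 10-item, 0–30 description itself proves that compression is scored. It does not: it shows only that nothing is left out of the sum. The item comes from the content of the named instrument, not from the text, so the point must stay conditional until the sponsor checks its form. That part of the objection stands. It does not dispose of the point, because the protocol adopts a named scale at its full length and the check is immediate.

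A reader might also infer that stocking wear worsens the score at both month 3 and month 6. The documents do not support that. TM at month 3 and SM at month 6 are reaching the end of assigned wear, and OM is in the same position at month 1.

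A further inference would be that the trial's non-inferiority conclusion is biased towards shorter compression. That is not supported either. The protocol attaches non-inferiority margins to recurrence and to the AVVQ at 12 months, not to the VCSS.

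It can be said that item-level scoring belongs in an analysis plan that is not shown. An exclusion could be recorded there, but the article positively defines the outcome as the full total. Baseline adjustment does not help, because the difference in wear arises after randomisation.

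On completion by patients, the blinded roles listed do not include a clinical examiner, so the protocol offers no ready substitute scorer.

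**Conclusion.** The point holds in conditional form. The text establishes that the full 10-item total is compared between arms, that no item is removed, that stocking duration is the randomised difference, and that unblinded patients complete the score. If the sponsor's form carries the standard compression item, the total counts assigned treatment as severity. OM versus SM at month 3 is then not interpretable as a comparison of disease.

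The shift is about 0.3 to 3 points on a 30-point scale. That range rests wholly on assumed adherence, off-schedule wear and item scores. Effects at month 1, at month 6, and in the TM contrasts at month 3 depend on visit timing or recall period. Assigned wear does not affect month 12, the recurrence outcome or the month-12 AVVQ test. The problem is confined to the earlier visits of one secondary outcome, but it is cheap to remove.

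**What to change.** Confirm on the trial's VCSS form whether one item scores use of compression. If it does, change the VCSS section as follows:

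- Compare arms on the score without that item (nine items, 0–27) at every visit.
- Report the compression item separately as a compliance measure, beside the diaries and questionnaires already planned.
- Keep the 0–30 total as descriptive only.

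The cost is one sentence in the outcome definition and one derived variable from items already collected. The small downside is that a 0–27 score is less comparable with 0–30 totals, which the descriptive total partly offsets.

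State also that patients who know their allocation complete the score, and interpret its between-arm differences with that limitation. Moving to scoring by a blinded examiner would be a separate decision and might need extra staff, since the protocol names none.

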#### Chronic Lower Limb Venous Insufficiency Questionnaire (CIVIQ)

The CIVIQ is an internationally recognized test for measuring the QoL of patients with chronic venous disease, 11, 12 which consists of 20 questions comprising four QoL domains: the pain (4 items), physical (4 items), social (3 items) and psychological (9 items) domains. Each question receives a score of 1–3 points (1 for mild and 5 for severe), and the overall score range from 0 to 100 points. These clinical studies reported only the overall outcome, 13 which indicates a patient’s QoL (24, 25).

#### Postoperative pain

The Visual Analog Scale (VAS, 0–10, 0 for no pain and 10 for the worst pain imaginable) will be used for the assessment of postoperative pain at 24 h and 30 days (26).

#### Postoperative complications

Postoperative complications (within 30 days) will include hematoma, ecchymosis, paresthesia, skin burns/paresthesia, phlebitis, infection, and DVT.

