### Statistical analysis

Analysis will follow the intention-to-treat (ITT) and per-protocol (PP) principles. Continuous outcomes (AVVQ score, VCSS, VAS score, and CIVIQ) will be analyzed using linear mixed models (LMMs) adjusted for baseline values, center, CEAP class, and time. Non-inferiority will be declared for the AVVQ score at 12 months if the upper limit of the 95% CI for the difference (OM-SM or TM-SM) is <*δ* (2.0 points). Recurrence rates will be compared using Kaplan-Meier survival analysis and Cox proportional hazards models. Complications will be compared using chi-square tests or Fisher’s exact tests. Compliance will be summarized descriptively. Subgroup analyses (e.g., by CEAP class, ablation type) are planned. Sensitivity analyses will be performed to assess the impact of missing data. SPSS version 21.0 will be used. *p* < 0.05 will be considered to indicate significance for superiority analyses.

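### Complications and VAS pain are assessed only up to about day 30, before assigned compression differs between arms, so they cannot inform the stated aim on complications at 12 months

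*Protocol article*

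**What the plan says.** - **Aim (Protocol article, Abstract, Background).** The trial is to determine the effects of 1, 3 and 6 months of compression "on recurrence, quality of life, and complications at 12 months after surgery".
- **Complications (Postoperative complications).** "Postoperative complications (within 30 days) will include hematoma, ecchymosis, paresthesia, skin burns/paresthesia, phlebitis, infection, and DVT". This is the only definition with a time window. The Objectives say complications are recorded in the three groups but give no window.
- **Pain (Postoperative pain).** The VAS "will be used for the assessment of postoperative pain at 24 h and 30 days". The Objectives give the VAS times as "at baseline, 24 h, and 1 month after surgery".
- **Intervention (Postoperation compression).** "All participants will have identical Class II (23–32 mmHg) full-length graduated compression stockings applied in the operating room immediately after ablation". The shortest assignment is "OM group: Wear stockings during waking hours for 1 month after surgery". The other arms (TM and SM) wear them for 3 and 6 months. The Abstract adds that all groups use the same stockings and follow the same wearing instructions.
- **Harms of long wear (Introduction).** "the long-term use of compression stockings can result in leg discomfort and skin irritation".
- **Analysis (Statistical analysis).** Complications are compared between arms by chi-square or Fisher's exact test.
- **Visits (Abstract, Follow-up).** Patients are seen at 1, 3, 6 and 12 months.

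**The concern.** An outcome can show an effect of duration only if it is observed after the durations have begun to differ. Here the arms separate at about 1 month, and both the complication window and the last VAS assessment close at that same point. Whatever the 30-day tables show, they cannot say whether longer wear causes or prevents complications.

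Two things are at stake. First, a stated aim of the trial cannot be answered by the outcome defined for it. Second, a null 30-day comparison could be taken as evidence that longer wear carries no added harm, although the comparison could not have detected any. The Discussion expects the results to feed directly into clinical practice guidelines. A recommendation on duration needs the harms of duration alongside recurrence and quality of life.

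**Working it through.** The plan gives no event rate, sample size or power for complications or pain, so there is no figure of its own to reproduce. The check sets the timing of exposure against the timing of assessment.

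**Step 1. Assigned exposure by period** (Postoperation compression)

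| Period | OM | TM | SM | Arms differ? | Complications counted? | VAS taken? |
|---|---|---|---|---|---|---|
| Days 0–30 | on | on | on | no | yes | 24 h, 30 days |
| Months 2–3 | off | on | on | OM v TM and SM | no | no |
| Months 4–6 | off | off | on | SM v OM and TM | no | no |
| Months 7–12 | off | off | off | past exposure only | no | no |

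Assigned wear in days 0–30 is 30 of 30 days in each arm, so each pairwise contrast is 30 − 30 = 0 days. For TM against SM, the arms stay identical until month 3.

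**Step 2. What the planned test can do in that window.** With the same assigned exposure, the expected 30-day event rate is the same in all arms. Three-arm chi-square tests were simulated with 200 per arm (Sample size and study duration), two-sided 5%, and common rates that are assumed because the documents give none:

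| Assumed common 30-day rate | Proportion of tests rejecting |
|---|---|
| 5% | 4.9% |
| 10% | 5.0% |
| 20% | 5.0% |

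The rejection rate equals the significance level whatever the rate. Power for an effect of duration is therefore nil, and a larger sample would not change this.

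**Step 3. What a later window could do.** For SM against OM, the normal approximation gives

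power = Φ[(|p1 − p2| − 1.96·se0) / se1], with se0 = √(2·p̄(1 − p̄)/n) and se1 = √((p1(1 − p1) + p2(1 − p2))/n).

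Here n = 200 per arm, or 200 × 0.8 = 160 after the protocol's 20% withdrawal. The event rates are assumptions for illustration:

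| Assumed rates (OM v SM) | n = 160 | n = 200 |
|---|---|---|
| 2% v 8% | 69.4% | 78.8% |
| 5% v 10% | 39.6% | 47.5% |
| 5% v 15% | 85.0% | 91.8% |
| 10% v 20% | 70.9% | 80.2% |

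A comparison after day 30 would be informative for sizeable differences and weak for small ones. The present window is informative for neither.

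**Step 4. Listed events against named harms.** The complication list has seven entries, mostly procedural or early postoperative events. Skin irritation and leg discomfort, the two harms the Introduction links to long wear, are not among them.

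**The case against.** **A 30-day window is conventional for procedural events.** Hematoma, ecchymosis and skin burns arise from the ablation itself, and 30 days is a reasonable period in which to describe them. This stands for those events. It is a reason to report them descriptively; it does not make them evidence on duration.

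**Late harms are recorded elsewhere.** A reader might infer that everything after the first month goes unmeasured. The documents do not support that. Adverse-event forms have no 30-day limit (Safety considerations), and major adverse events run through follow-up. AVVQ, VCSS and CIVIQ are compared to 12 months and may reflect discomfort; CIVIQ has a pain domain, although its section refers only to the overall score. Compliance is also tracked. The Abstract and Objectives mention complications without a window, and the assessment schedule in Figure 2 is not shown. What remains is narrower. Adverse-event forms are a reporting duty with no between-arm comparison described, major adverse events cover only myocardial infarction, stroke and death, and no defined complication outcome is compared after day 30.

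**Does the same flaw reach the quality-of-life models?** The models are described as "linear mixed models (LMMs) adjusted for baseline values, center, CEAP class, and time". A reader might infer that, without a group-by-time term, the AVVQ difference averages in visits at which the arms were still identical and is pulled toward zero. That does not follow. The same section fixes the AVVQ non-inferiority claim at 12 months. The phrase lists adjustment terms and does not even name treatment group, so it is not a full model, and the interaction may properly sit in an analysis plan.

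**Are false positives a problem?** Seven independent tests at 5% would give 1 − 0.95^7 = 30% for at least one false finding. The documents do not support that as an estimate: hematoma and ecchymosis are unlikely to be independent, paresthesia appears in two entries, and Fisher's test is conservative for rare events.

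**The trial is open-label.** Knowing the assigned duration could alter reporting or adherence before day 30. That could produce a difference, but not one caused by duration worn.

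**Conclusion.** The point holds. As defined, 30-day complications and VAS pain are observed under an assigned contrast of 0 days, and the planned tests of complications have no power for an effect of duration. The 30-day window contradicts the Abstract's aim of complications at 12 months, and the harms the Introduction attributes to long wear are not listed outcomes. The conclusion rests only on the protocol's own timings and on assigned rather than actual wear. The simulated rejection rates use assumed event rates but do not depend on them materially; the power figures for a later window are illustrations.

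This should be fixed, but it does not undermine the trial as a whole. Complications and pain are secondary, with no success criterion and no role in the sample size. Recurrence and quality of life are followed to 12 months, so it would be too strong to say the trial cannot weigh benefit against burden at all.

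**What to change.** 1. Reconcile the Abstract aim, the Objectives and the complications definition so that they state one set of windows.
2. At the existing 3-, 6- and 12-month visits, record the complications that can occur later (for example DVT, phlebitis, infection, paresthesia), together with stocking-related skin irritation and leg discomfort, each with a short definition.
3. Make events after day 30 the between-arm comparison for complications.
4. Report 30-day complications and VAS pain descriptively by arm, as outcomes of the procedure, and say that they are not evidence on duration. VAS at 3 and 6 months is optional.

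The cost is a few case-report fields at visits already planned and some wording in the analysis section. The limitation is that reports of discomfort and irritation will come from patients who know their assigned duration, which should be acknowledged when they are interpreted. The change is best made early, since symptoms not asked about at a visit cannot be recovered reliably afterwards.
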